### 2.4. Eligibility

#### 2.4.1. Inclusion Criteria

Clinical diagnosis of COPD according to GOLD [1].Ability to offer written authorization or nominate a person to read the Statement of Free and Informed Consent, giving the research patient’s agreement.Patients over 65 years of age with preserved cognitive function according to the Mini-Cog, that is, those who scored at least 3 to 5 points [30].Absence of exacerbation and stability of drug treatment in the last month.A 3-month absence from participation in a pulmonary rehabilitation program.

#### 2.4.2. Exclusion Criteria

Patient with a previous medical diagnosis of a disease that affects cognitive function and inhibits understanding of the questionnaires.Patients unable to perform any of the assessments.Previous acupuncture therapy.Being, or having been, in a rehabilitation group in the last 3 months before starting the protocol.Patients who present an exacerbation of the clinical condition during the collection period will be excluded.

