## 2. Materials and Methods

### 2.1. Design

The study will be a two-arm, parallel-group, prospective, computer-randomized, controlled, evaluator-blind design lasting for 16 weeks (two eight-week intervention periods). The study was registered on the www.ensaiosclinicos.gov.br (accessed on 23 May 2022) (REBEC) website. The protocol has been developed according to the SPIRIT guidelines [26] and described according to the CONSORT statements [27]. The acupuncture protocol will follow the recommendations of the Standards for Reporting Interventions in Clinical Trials of Acupuncture (STRICTA), a formal extension of CONSORT. STRICTA was designed to improve the integrity and transparency of reporting interventions in clinical trials of acupuncture so that such trials can be more accurately interpreted and easily replicated [28]. Furthermore, the intervention will be reported according to the Model for Intervention Description and Replication (TIDieR) checklist and guide [29].

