### 2.3. Randomization

Randomization will be generated by a website (https://www.randomizer.org/ (accessed on 23 May 2022)) and performed by a researcher not involved in the recruitment, treatment, or evaluation of patients. This investigator will be instructed not to disclose the scheduled intervention to the other investigators until the completion of the study. Since randomization will occur after the initial evaluation, it is characterized as a blind distribution. The sequence will be generated in blocks of four patients in random order. The allocation will be hidden in numerical sequence, in opaque sealed envelopes.

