##### Saint George’s Respiratory Questionnaire (SGRQ)

The SGRQ addresses aspects related to three domains: symptoms, activity, and psychosocial impacts that respiratory disease inflicts on the patient. Each domain has a maximum possible score; the points for each answer are added up and the total is referred to as a percentage of the maximum. A total score is calculated from 0 (no health impairment) to 100 (maximum health impairment). In addition to the total score, there is also a score for each domain of symptoms, activity, and impact, which are also scored from 0 to 100. Values above 10% reflect an altered QOL in that domain. Changes equal to or greater than 4% after an intervention, in any domain or the total number of points, indicate a significant change in the patients’ QoL [35].

The SGRQ will be used to assess QoL, which will be analyzed in Phase I and at the ends of Phase II and Phase III.

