### 2.8. Analyses

Statistical analysis will be performed following the intention-to-treat principle. Data will be analyzed using the SPSS Statistics statistical package (v.22.0; IBM Corp, Armonk, NY, USA). The normality of the data will be verified using the Kolmogorov-Smirnov test and the homoscedasticity of the data through the Levene test. The parametric data will be expressed as mean and standard deviation. In the case of nonparametric data, the median and its upper and lower limits will be expressed. The data will be analyzed using generalized linear mixed-effects models for repeated measures with post hoc Bonferroni analysis for correction. For all tests, an alpha of 5% will be adopted. Effect sizes will be interpreted based on their minimal clinically important differences (MCIDs).

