Our work predicts a score of 8 on the PEDro scale as we plan to specify eligibility criteria, randomly assign patients, and use veiled subject allocation by a researcher designated exclusively for this role during research planning, performed using a computer program; we will have well-defined inclusion and exclusion criteria ensuring similar groups with regard to the most important prognostic indicators at baseline; and there will be blinding of the evaluators who will measure the outcomes. Furthermore, we will aim to ensure patient adherence, ensuring that measurements of at least one key outcome will be obtained in more than 85% of subjects initially distributed among the groups, using weekly telephone calls made to patients in the control group; data will be analyzed by intent to treat; we will describe the results of intergroup statistical comparisons in at least one key result; and we will describe measures of precision as measures of variability for at least one key outcome. We will lose in points that do not apply to studies with acupuncture, i.e., blinding of subjects and blinding of the therapist who will apply the therapy. In addition, we will follow up for a total of 16 weeks by reapplying the tests and questionnaires at 8 weeks, which will enable assessment of the responses in the short and long term, which, according to our previous review, has not yet been undertaken.

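### Excluding patients who exacerbate during data collection removes randomised patients on an outcome-related event and contradicts the intention-to-treat analysis

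*Protocol article*

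**What the plan says.** - **Exclusion (section 2.4.2):** "Patients who present an exacerbation of the clinical condition during the collection period will be excluded". The collection period is not defined.
- **Entry criterion (section 2.4.1):** a separate condition requires "Absence of exacerbation and stability of drug treatment in the last month".
- **Timing of randomisation (section 2.3):** "Since randomization will occur after the initial evaluation, it is characterized as a blind distribution".
- **Outcome collection (section 2.6.1, SGRQ):** quality of life is "analyzed in Phase I and at the ends of Phase II and Phase III". With two eight-week periods (section 2.1), that means baseline, week 8 and week 16. The PGI follows the same schedule.
- **Analysis principle (section 2.8):** "Statistical analysis will be performed following the intention-to-treat principle". The Discussion repeats it ("data will be analyzed by intent to treat") and counts it towards the predicted PEDro score.
- **Missing data (subsection on lost data under 2.8):** dropouts for lack of efficacy or adverse effects are treated as not at random and singly imputed. Losses unrelated to any measure go into the mixed model. Exclusion for exacerbation is not mentioned.
- **Contact with patients:** the acupuncture arm attends three times a week (Abstract). For controls, the Discussion describes a retention measure, "using weekly telephone calls made to patients in the control group".

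**The concern.** Two of the three outcome assessments fall after randomisation, so an exclusion that runs through data collection acts on patients already allocated. An exacerbation is a worsening of the disease whose impact the SGRQ, PGI and CAT measure, so those removed would be expected to score worse. Allocation may also affect how often exacerbations occur and how often they are noticed.

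The groups analysed would then no longer be the groups randomised, and the bias can go either way. If acupuncture prevents exacerbations, that benefit is deleted. If closer contact brings more exacerbations to light in the acupuncture arm, more of its sicker patients are removed and acupuncture looks better than it is. With no sham and with unblinded patients and therapists, the trial depends heavily on keeping the randomised comparison intact.

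**Working it through.** **1. Does the rule reach past randomisation?** Sections 2.3, 2.1 and 2.6.1 give this order: baseline evaluation, randomisation, week 8 collection, week 16 collection. An undefined collection period naturally covers all three collections. The criterion just before this one in section 2.4.2 is expressly tied to the time before the protocol starts; this one is not.

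**2. Is there a rule that keeps these patients in the analysis?** No. They fit neither missing-data category by name. The options give very different results: deletion; use of earlier visits only in the mixed model; or, if they were classed as treatment failures, the worst possible value, which for the SGRQ is 100.

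**3. How many patients could be affected?** The article gives no rate. Assuming a constant rate r per patient-year, the proportion with at least one event in 16 weeks is 1 − exp(−r × 16/52):

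| r (assumed) | Proportion |
|---|---|
| 0.3 | 8.8% |
| 0.5 | 14.3% |
| 1.0 | 26.5% |
| 1.5 | 37.0% |

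The 20% loss allowance in section 2.2 is passed when r exceeds −ln(0.8) × 52/16 = 0.73 per year.

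**4. Bias from unequal detection, no true effect (all inputs assumed).** Suppose 30% exacerbate in each arm, all are detected with acupuncture and half in control, and an exacerbation worsens the SGRQ by 10 points. No exacerbators remain in the acupuncture arm. Among controls, 15% of the arm remain as undetected exacerbators out of 85% retained: (0.15 / 0.85) × 10 = 1.76 points worse. Section 2.6.1 takes 4 points as a meaningful change.

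**5. Bias when acupuncture halves exacerbations and does nothing else (assumed; worsening of 0.5 to 1.0 SD).**
- 20% versus 10%: the all-randomised difference is 0.10 × 0.5 to 0.10 × 1.0 = 0.05 to 0.10 SD.
- 30% versus 15%: 0.15 × 0.5 to 0.15 × 1.0 = 0.075 to 0.15 SD.
- After excluding exacerbators: 0 in both cases.

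**6. Power.** The planned 50 per group does not reproduce from the inputs in section 2.2 (effect size 0.59, alpha 5%, power read as 80%). A two-sided t-test needs 47, or 47/0.8 = 59 after 20% loss; a one-sided test needs 37, or 37/0.8 = 47. That is a separate matter. Taking 50 per group as given, two-sided t-test power at 0.59 is 0.83 with all 50 analysed. With exclusions:

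| Excluded per arm (assumed) | n, no other loss | Power | n, with 20% loss as well | Power |
|---|---|---|---|---|
| 0% | 50 | 0.83 | 40 | 0.74 |
| 10% | 45 | 0.79 | 36 | 0.70 |
| 20% | 40 | 0.74 | 32 | 0.64 |
| 30% | 35 | 0.68 | 28 | 0.58 |

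The Discussion aims to measure at least one key outcome in more than 85% of those randomised. Excluding 15% or more before any follow-up measurement would miss that aim.

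**The case against.** The best defence is that the sentence stands among the eligibility criteria and may concern only baseline data collection. A patient could satisfy the one-month criterion and then exacerbate during Phase I testing. The overlap with the inclusion criterion does not settle the meaning either, because the rehabilitation criterion also appears in both lists. That part stands: redundancy is weak evidence, and the conclusion here rests on the schedule of outcome collection instead. If only baseline is meant, the text still has to say so, because staff applying it as printed would remove randomised patients.

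Second, exclusion might mean withdrawal from the protocol with data retained under section 2.8. This is possible, but nothing says it, and the missing-data rules do not name the case.

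Third, the numbers are assumed, and some lean high. The article does not say how exacerbations are ascertained, and controls are also seen at weeks 8 and 16. Events missed by weekly calls would probably be milder than those detected. Variation between patients lowers the proportion with at least one event at a given mean rate. With equal detection and no true effect, the bias in step 4 is zero. The 20% allowance may already include these exclusions, in which case the columns without other loss are the relevant ones. All of this limits the weight of the figures. It does not remove the contradiction.

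**Conclusion.** The concern holds. On its natural reading, section 2.4.2 removes randomised patients for a post-randomisation, outcome-related event, which is incompatible with the intention-to-treat analysis stated in section 2.8 and the Discussion. The missing-data subsection does not resolve the conflict.

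The actual size of the bias cannot be computed, because the article gives no exacerbation rate, detection rate or effect of exacerbation on the SGRQ. Under the stated assumptions it could approach half of the 4-point threshold in favour of acupuncture, or wipe out a real benefit of up to 0.15 SD. Exclusions could also exceed the whole loss allowance. The contradiction depends on none of these assumptions.

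**What to change.** - Limit the exacerbation exclusion in section 2.4.2 to the time before randomisation.
- State that every randomised patient remains in follow-up and in the primary analysis whether or not an exacerbation occurs, and reconcile sections 2.4.2 and 2.8 and the missing-data subsection accordingly, including how an exacerbation is handled there.
- Record exacerbations by the same method in both arms, for example the same weekly question, and report them by arm.
- If wanted, repeat the primary analysis without exacerbators as a supplementary analysis only.

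Whether sessions continue during an exacerbation is a clinical decision and is not addressed here.

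The cost is small: a one-sentence change to the eligibility criteria, a short addition on handling in the analysis section, and one question at existing contacts. Assessments due within 48 hours of the last session (section 2.5) may coincide with an exacerbation, so the outcome data will be somewhat noisier. The change should come early, because outcomes not collected after an exclusion cannot be recovered.

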### 2.5. Intervention

The tests and questionnaires applied after phases II and III will be carried out within 48 h after the last session.

The period for carrying out this protocol will be from 2022 to 2025. Figure 1 presents the flow chart of the full study protocol.

#### Acupuncture

Acupuncture needles made of stainless steel, 0.25 mm gauge and 3 cm long, approved by the Brazilian National Health Surveillance Agency (ANVISA) will be used.

The description of the technique and methodology follows the principles suggested by the Standards for Reporting Interventions in Clinical Trials of Acupuncture (STRICTA) [28], described below:(a)the Traditional Chinese Medicine needling style will be used, based on the literature in the area and clinical consensus.(b)treatment reasoning will be based on Chinese acupuncture literature, consensual methods, and literary references.(c)the selection of needling points will not change throughout the treatment.(d)the needling will be manual.

After the insertion of needles, manipulation will be carried out with adequate stimulus to obtain Dé Qi (acupuncture sensation) at determined and preestablished points for all patients.

The procedure for each session will be as follows:

Patients in the supine position will have the needles removed 30 min after the last needle is inserted.

The following acupoints will be used:Zusanli-stomach 36 (ST36 bilateral).Xuehai-spleen 10 (SP10 bilateral)Qihai-Ren Mai 6 (RM6 or CV6).Danzhong–Ren Mai 17 (RM17 or CV17).Chize-lung 5 (LU5 bilateral).Lieque-lung 7 (LU7 bilateral).

A total of 10 needles will be used per session.

After a thorough evaluation (Hsieh and colleagues, 2020) of the acupoints used in prior randomized clinical trial studies for COPD therapy, the points were chosen. Furthermore, sites were chosen that allows the patient to remain supine during treatment without changing positions [31].

The order of puncture will follow the traditional concept of needling. Because the problem (COPD) is at the top (lungs), the puncturing starts from the bottom. Thus, the order of puncture will follow the sequence: ST36, SP10, RM6, RM17, LU5, and LU7.

### 2.6. Outcome Measures

The primary outcome (quality of life) will be assessed using the SGRQ and PGI questionnaires. Secondary outcomes will be evaluated using DEXA, Spirometry, 6MWT, LCADL, and CAT.

#### 2.6.1. Questionnaires, Scales and Tests

##### Mini-Cog

The Mini-Cog will be applied only in the first phase of the experiment, as an inclusion criterion for patients over 65 years of age. The test consists of a three-word memorization task and a clock drawing task. The individual must be able to remember the three words after making the drawing, scoring 1 point for each word they remember and 2 points for correctly drawing the clock [30,32].

The Mini-Cog has a total score of 5 points. Results ranging from 3 to 5 points are considered normal [32].

##### Double Energy X-ray Absorptiometry (DEXA)

Total body mass, fat mass, lean mass, bone mineral density, and height will be evaluated using dual-energy radiological absorbance (DEXA) (Lunar Radiation Corporation, Madison, WI, USA, DPX model). Fat mass and lean mass will be evaluated by total body analysis and by body segment (upper, lower and trunk). For this analysis, patients will be positioned in the scanning area of the equipment so that the sagittal line marked on the equipment passes under the center of certain anatomical points such as the skull, spine, pelvis, and lower limbs. Patients will be evaluated wearing light clothes, without the use of any metal object that could interfere with the measurements.

DEXA will be used to characterize the sample and to assess changes in the subjects’ body composition. Therefore, it will be evaluated in Phase I and at the end of Phase III.

##### Spirometry

Spirometry is the measurement of the air that enters and leaves the lungs [33,34]. Spirometry is a test that enables the diagnosis and quantification of ventilatory disorders. It will be used to assess the individual’s pulmonary function and characterize the studied sample according to the GOLD criteria [1].

Spirometry will be performed using the MIR Spirometer, Model Minispir, manufactured by MIR Medical International Research (Rome, Italy), with the individual sitting with trunk support, with arms along the body and wearing a nose clip. The subject will be asked to place the mouthpiece above the tongue and close the mouth tightly around it; at the researcher’s command, the individual will make a deep inspiration until total lung capacity (TLC) has been reached, followed by a “fast and prolonged” forced expiration, until the examiner’s end signal, when the patient will make another maximum inspiration with the mouthpiece still in the mouth. At least three measurements will be performed, three of which are acceptable and two reproducible, for evaluation; the best values will be recorded according to the 1st Brazilian Consensus on Spirometry. The test will analyze forced vital capacity (FVC); forced expiratory volume in the first second (FEV1); forced expiratory flows at 25%, 75%, and 25–75% of the FVC curve; peak expiratory flow (PEF); the relationship between FEV1 and FVC (FEV1/FVC); and inspiratory capacity (IC), which is the amount of air that can be inhaled from resting expiratory level to TLC. These parameters will be expressed in absolute values and percentage of the predicted value, according to the GOLD reference values [1].

The spirometer will be calibrated each day before the tests. Calibration will involve measuring the output of the spirometer and the sensitivity of the recording device or generating a software correction factor, and it will therefore involve tuning the equipment for performance within certain limits. For this purpose, a 3 L syringe supplied by the manufacturer will be used along with the equipment.

Spirometry will be applied in Phase I to confirm the diagnosis according to GOLD and characterize the sample, and at the end of Phase II and Phase III to evaluate the response to the acupuncture intervention.

##### Patient-Generated Index (PGI)

The PGI is completed in three steps: (1) Patients identify the five most important areas of their life affected by the disease, in this case, chronic obstructive pulmonary disease; (2) patients rate how much each area was affected by COPD using a scale of 0 to 6, where 0 is the worst imaginable and 6 is exactly how they would like it to be; (3) patients now imagine they have 10 “tokens” to spend on improving selected areas and allocate these tokens to areas according to their priority. An overall index is then calculated by multiplying the ratings for each area in Step 2 by the proportion of tokens given to that area in Step 3, which are then added to produce an index where higher scores indicate higher QoL [14].

It is worth mentioning that for the PGI there is a minimum detectable difference of 10.8 [14].

The PGI will be used to assess QoL, which will be analyzed in Phase I and at the ends of Phase II and Phase III.

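### The PGI score as printed runs from 0 to 6, so its stated benchmark of 10.8 lies outside any possible difference and cannot be on the same scale

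*Protocol article*

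**What the plan says.** Section 2.6 (Outcome Measures) states: "The primary outcome (quality of life) will be assessed using the SGRQ and PGI questionnaires".

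The PGI subsection of 2.6.1 gives the scoring in three steps and a formula:

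- Step 1: "Patients identify the five most important areas of their life affected by the disease".
- Step 2: each area is rated "using a scale of 0 to 6, where 0 is the worst imaginable and 6 is exactly how they would like it to be".
- Step 3: "patients now imagine they have 10 “tokens” to spend on improving selected areas".
- The index comes from "multiplying the ratings for each area in Step 2 by the proportion of tokens given to that area in Step 3" and adding the products. Higher scores mean better quality of life.

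The next paragraph, citing the same source as the scoring, remarks that "for the PGI there is a minimum detectable difference of 10.8". No unit, score range or conversion to a percentage is given for the PGI.

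Section 2.8 (Analyses) adds the interpretation rule: "Effect sizes will be interpreted based on their minimal clinically important differences (MCIDs").

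**The concern.** A sum of ratings weighted by proportions is a weighted mean, so it stays on the scale of the ratings. A benchmark of 10.8 on a scale that ends at 6 signals either that a step is missing from the formula or that the figure was taken from a differently scaled version of the index.

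What is at stake is how one of the two primary-outcome instruments will be interpreted. Section 2.8 commits the authors to reading effects against a clinical threshold, and for the PGI the article supplies one figure only. If that figure cannot be used on the score as defined, the yardstick has to be settled later. If that happens after the results are known, the choice is open to the charge of having been made to suit them.

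There is also a mismatch of labels. The PGI subsection calls 10.8 a minimum detectable difference, while section 2.8 calls for MCIDs. These are different quantities, and the article names no MCID for the PGI.

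**Working it through.** **Inputs, all from the PGI subsection of 2.6.1**

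- Five areas, i = 1 to 5.
- Rating r_i between 0 and 6.
- Tokens t_i, ten in total, so the proportion is p_i = t_i / 10 and the proportions sum to 1 (or less, if a patient leaves tokens unspent).
- Stated benchmark: 10.8, without a unit.

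**Can the plan's figure be reproduced?** No. 10.8 is a cited constant and the article gives no inputs for it. It can only be compared with the attainable range of the score.

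**Step 1: range of the index as printed**

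PGI = r_1·p_1 + … + r_5·p_5

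- Upper bound: every r_i = 6 gives 6 × (p_1 + … + p_5) = 6 × 1 = 6.
- Lower bound: every r_i = 0 gives 0.

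Enumerating every way of dividing ten tokens over five areas at the extreme ratings gave the same result: minimum 0.0, maximum 6.0.

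**Step 2: compare with the benchmark**

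- Largest possible change in a patient, or difference between group means: 6 − 0 = 6.
- 10.8 / 6 = 1.8, so the benchmark is 1.8 times the largest possible difference.
- Equivalently, 6 / 10.8 = 0.556: a move from worst to best on every area covers 56% of the benchmark.

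**Step 3: what 10.8 would mean on other scales**

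The article states neither of these scales; both are assumptions.

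| Assumed scale of 10.8 | How it would arise | Share of that range | Equivalent on the printed 0 to 6 scale |
|---|---|---|---|
| 0 to 100 | printed index / 6 × 100 | 10.8 / 100 = 10.8% | 10.8 × 6 / 100 = 0.648 |
| 0 to 60 | raw token counts in place of proportions | 10.8 / 60 = 18% | 10.8 / 10 = 1.08 |

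The benchmark is attainable under either assumption, but the two equivalents differ by a factor of 1.08 / 0.648 = 1.67. A reader therefore cannot pick a repair from the article alone.

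**Step 4: what is not affected**

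- Both candidate repairs multiply the score by a constant (100/6 or 10). In a linear mixed model on the score, the estimated difference and its standard error are multiplied by the same constant, so test statistics, p-values and standardised effects do not change.
- Section 2.2 bases the sample size on the SGRQ total score, with an effect size of 0.59. The PGI does not enter it.

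**Step 5: compare with the other primary instrument**

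The SGRQ subsection gives a 0 to 100 score, expressed as a percentage of the maximum, and a 4% change as its threshold. Score and threshold are on one scale there. The PGI subsection has no such statement.

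**The case against.** The strongest reply is that this is a condensed account of an established instrument. The scoring and the 10.8 carry the same citation, so a conversion step has probably dropped out of the summary, and the working protocol may contain it. The article also introduces 10.8 as a remark in passing. It attaches no responder definition, success criterion or decision rule to it, in contrast with the SGRQ, where a change of 4% or more is said to indicate a significant change.

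Much of this stands, and it limits the consequence. A reader might infer that every PGI effect, however large, will be judged below threshold, or that the trial cannot show a benefit on the PGI. The documents do not support that. The article never says that PGI results will be declared positive or negative against 10.8, and it calls the figure a minimum detectable difference, not an MCID. Its use for interpretation is an inference from section 2.8. Nor is there evidence that the trial will in fact score the PGI on 0 to 6.

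A reader might also take 10.8 to be a detectable change for a single patient, reflecting measurement error. The article does not say whether the figure applies to individuals or to groups, nor how it was derived.

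The appeal to condensation does not remove the mismatch itself. The article did not leave the scoring to another document: it printed a complete formula and a numerical benchmark in adjacent paragraphs, and the two are incompatible. This is a contradiction within the text, not a missing detail.

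**Conclusion.** The point holds in a limited form. As printed, the PGI runs from 0 to 6, and the benchmark of 10.8 is 1.8 times the largest difference that the score allows. The scoring rule and the benchmark cannot be on the same scale. Because 10.8 is the only PGI benchmark in the article and section 2.8 promises interpretation against MCIDs, the PGI half of the primary outcome has no usable interpretation threshold as written.

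The range of 0 to 6 and the ratio of 1.8 follow from the printed scoring rule and need no assumption. The equivalents of 0.65 and 1.08 each rest on an assumed scale that only the cited source can confirm. The statement that significance tests are unaffected assumes that whatever step is missing is a linear rescaling. The damage is to interpretation; the sample size, the randomisation and the data collected are untouched.

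**What to change.** Before outcome data are seen, state one scale for the PGI score and its benchmark, and check both against the cited source. There are two routes:

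1. Add the missing step to the formula. If the source has 10.8 on 0 to 100, divide the printed index by 6, multiply by 100, and give the range as 0 to 100.
2. Keep the 0 to 6 index and convert the benchmark: about 0.65 if 10.8 is on 0 to 100, about 1.08 if it is on 0 to 60.

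In either case, give the unit and range beside the figure. In section 2.8, do not treat 10.8 as an MCID unless the source supports that use. Otherwise report it under the name that the PGI subsection gives it, and say which MCID, if any, will be used for the PGI.

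The cost is about one line in the PGI subsection and one in section 2.8, plus a look at the cited source. Data collection, sample size and the analysis model stay as they are.
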